# Reducing the rate and duration of Re-ADMISsions among patients with unipolar disorder and bipolar disorder using smartphone-based monitoring and treatment – the RADMIS trials: study protocol for two randomized controlled trials

**DOI:** 10.1186/s13063-017-2015-3

**Published:** 2017-06-15

## Abstract

**Background:**

Unipolar and bipolar disorder combined account for nearly half of all morbidity and mortality due to mental and substance use disorders, and burden society with the highest health care costs of all psychiatric and neurological disorders. Among these, costs due to psychiatric hospitalization are a major burden. Smartphones comprise an innovative and unique platform for the monitoring and treatment of depression and mania. No prior trial has investigated whether the use of a smartphone-based system can prevent re-admission among patients discharged from hospital. The present RADMIS trials aim to investigate whether using a smartphone-based monitoring and treatment system, including an integrated clinical feedback loop, reduces the rate and duration of re-admissions more than standard treatment in unipolar disorder and bipolar disorder.

**Methods:**

The RADMIS trials use a randomized controlled, single-blind, parallel-group design. Patients with unipolar disorder and patients with bipolar disorder are invited to participate in each trial when discharged from psychiatric hospitals in The Capital Region of Denmark following an affective episode and randomized to either (1) a smartphone-based monitoring system including (a) an integrated feedback loop between patients and clinicians and (b) context-aware cognitive behavioral therapy (CBT) modules (intervention group) or (2) standard treatment (control group) for a 6-month trial period. The trial started in May 2017. The outcomes are (1) number and duration of re-admissions (primary), (2) severity of depressive and manic (only for patients with bipolar disorder) symptoms; psychosocial functioning; number of affective episodes (secondary), and (3) perceived stress, quality of life, self-rated depressive symptoms, self-rated manic symptoms (only for patients with bipolar disorder), recovery, empowerment, adherence to medication, wellbeing, ruminations, worrying, and satisfaction (tertiary). A total of 400 patients (200 patients with unipolar disorder and 200 patients with bipolar disorder) will be included in the RADMIS trials.

**Discussion:**

If the smartphone-based monitoring system proves effective in reducing the rate and duration of re-admissions, there will be basis for using a system of this kind in the treatment of unipolar and bipolar disorder in general and on a larger scale.

**Trial registration:**

ClinicalTrials.gov, ID: NCT03033420. Registered 13 January 2017. Ethical approval has been obtained.

**Electronic supplementary material:**

The online version of this article (doi:10.1186/s13063-017-2015-3) contains supplementary material, which is available to authorized users.

## Background

Unipolar disorder and bipolar disorder are common mental diseases with a lifetime prevalence of 15–20% and 1–2%, respectively [1, 2]. Unipolar disorder and bipolar disorder combined account for nearly half of all morbidity and mortality due to mental and substance use disorders [3] and burden society with the highest health care costs of all psychiatric and neurological disorders [4].

Although psychiatric treatment internationally, and in Denmark, has shifted more from inpatient treatment to outpatient treatment during recent decades, costs due to psychiatric hospitalization are still a major burden comprising two thirds of all direct costs in the five Regions of Denmark [5]. Patients with affective disorders are more frequently hospitalized than any other patient group, counting more than 10,800 patients in 2013 among the entire Danish population of 5.4 million people, and 20% of all psychiatric hospitalizations in Denmark [6]. The cost of these hospitalizations alone is estimated to be DKK648 million (approximately €8.7 million) per year in Denmark (10,800 hospitalizations with a mean of 20 days’ stay for a cost of 3000 DKK/day (€400)). The discharge period after hospitalization is a high-risk period with a more than 300 times increased risk of suicide during the first week [7] and a high risk of re-admission [8, 9]. Patients are often afraid of leaving the hospital, feeling alone with the prospect of an appointment with a physician 1 or more months ahead. A pilot study from our group in which 45 patients discharged from psychiatric hospital self-monitored symptoms using a daily computer-based self-monitoring system emphasized the pivotal importance of continued contact with a clinician such as a nurse [10]. Smartphones comprise a unique platform for the monitoring and treatment of depression and mania. Depression and mania are associated with changes in several behavioral components (e.g., reduction in activity level, change in speech) and motivational states (e.g., anhedonia), some of which may be detectable using readily available smartphone sensors [11–13]. Prior work done by our group has developed and tested a unique smartphone-based system for the treatment of bipolar disorder (the MONARCA system) [14, 15]. The MONARCA system is capable of collecting subjective self-assessment data and automatically generated objective smartphone data from patients on a daily basis while allowing simple bidirectional communication between clinicians and the patients [15]. We find it likely that daily contact with a psychiatric hospital nurse using a bidirectional feedback system combined with objective smartphone-based early warning signs, assessed using a smartphone app, will reduce the risk of re-admission and the risk of relapse of depressive and (hypo)manic symptoms.

Treatment of unipolar disorder and bipolar disorder applies a variety of methods, including antidepressants, mood stabilizers, psychoeducation, and cognitive behavioral psychotherapy (CBT).

CBT has proven efficacious in the treatment and prevention of depressive episodes in unipolar disorder [16], but the effect in relation to bipolar disorder is controversial [17]. Depressive symptoms dominate bipolar disorder as 80% of episodes are depressive [18], but bipolar depression is difficult to treat as only a few drugs have proven effects [19] and psychological interventions have proven ambient effects on depressive symptoms revealing positive effects in some studies [20–22], but not in others [23–25]. Specifically targeting depressive rumination, rumination-focused cognitive therapy and concreteness training (a facilitated self-help intervention intended to increase specificity of processing in patients with depression) have shown encouraging results in the treatment of residual depression [26]. However, the number of CBT therapists is very low compared with the huge demand for CBT. Internet- and computer-based CBT systems exist and have been proved effective in relation to depression [27]. Recently, CBT has been suggested for smartphones [28] but the effect has never been tested in a randomized controlled trial (RCT).

In the RADMIS trial we will develop a smartphone-based CBT program that includes methods to relieve depressive ruminations [23, 29]. The smartphone-based system used in the RADMIS trials is inspired by the MONARCA system (see below), and is called the Monsenso system. By using the sensing, computational and communication capabilities of smartphones, it is possible to continuously monitor an individual’s context including physical activity, location, and environment. Thus, smartphones hold significant promise as a platform to monitor behavioral and environmental indicators of depression and mania and for treatment, facilitating early intervention and smartphone-based CBT.

Prior research on using smartphones in the detection of unipolar disorder and bipolar disorder has shown promising but preliminary results. A small study on eight patients with depression (not including a control group) found that sensor data from smartphones could detect social patterns [30]. Another study found that sensors from smartphones were effective at detecting social and sleep behaviors among patients with depression [31].

The MONARCA system, developed and tested by our group [14, 15], has been proved highly usable and useful by patients with bipolar disorder with a high self-assessment adherence (87–95%), and was considered to help patients to better manage their disease [32]. A study investigating the effect of the MONARCA system (daily self-monitoring including a two-level feedback loop to clinicians) in a RCT found no overall effect in primary analyses but secondary analyses suggested that the system was able to reduce manic symptoms, but may sustain depressive symptoms in patients with bipolar disorder [33]. These results are in accordance with the findings that psychological interventions for bipolar disorder in general have more effect on manic than depressive symptoms and more effect on preventing that treating acute depression [23–25]. Consequently, emphasis on depressive symptoms should be a high priority including considerations on mechanisms to reduce the negative processing bias and depressive ruminations in patients with unipolar disorder and bipolar disorder [23, 33].

Finally, research by our group found that automatically generated objective smartphone data reflect illness activity in patients with bipolar disorder. Data on physical activity (the number of changes in cell tower ID/day), social activity (the number and duration of phone calls/day and the number of text messages/day) [11–13] and voice features collected during phone calls [34] correlated significantly with the severity of clinically rated depressive and manic symptoms. Although these findings are encouraging and innovative, there is a need to integrate self-monitored smartphone data with automatically generated objective smartphone data on physical and social activity, as well as speech and sleep, into a composite smartphone-generated electronic measure. This composite measure should be modeled to have a high correlation with depressive and manic symptoms, and a high predictive ability to identify upcoming affective episodes for the individual patient in order to facilitate early intervention.

### Hypotheses

Using a smartphone-based monitoring and treatment system for daily electronic self-monitoring, including an integrated feedback loop, on both subjective and automatically generated behavioral data on measures of illness activity (phone usage, social activity, physical activity, mobility, voice recognition and sleep) and context-aware CBT modules, the Monsenso system, reduces the rate and duration of re-admission more than standard treatment in adult patients with unipolar disorder or bipolar disorder, respectively, being discharged from hospital.

### Objectives

To investigate in two individual, randomized controlled, single-blind, parallel-group trials whether the use of a smartphone-based monitoring and treatment system, including an integrated feedback loop, on both subjective and automatically generated behavioral data on measures of illness activity (phone usage, social activity, physical activity, mobility, voice recognition and sleep) and context-aware CBT modules, the Monsenso system, reduces the rate and duration of re-admissions more than treatment-as-usual in adult patients with unipolar disorder or bipolar disorder, respectively.

Further, to investigate if the Monsenso system reduces the severity of clinically rated affective symptoms and the number of affective episodes, improves psychosocial functioning, quality of life, severity of self-assessed affective symptoms, recovery, empowerment, adherence to medication, wellbeing, and satisfaction with care, and reduces perceived stress, rumination and worrying more than standard treatment without a smartphone-based system in adult patients with unipolar disorder or bipolar disorder, respectively.

Data will be collected and analyzed separately according to psychiatric diagnosis (unipolar disorder and bipolar disorder).

## Methods

The present trial protocol is reported according to the CONsolidated Standards Of Reporting Trials (CONSORT) Statement and Standard Protocol Items: Recommendations for Interventional Trials (SPIRIT) [35–37] (Fig. 1, Additional file 1).

**Fig. 1 Fig1:**
[figure not shown]
Schedule of enrolment, interventions, and outcome assessments in the RADMIS trials

The trial protocol describes two individual, randomized controlled, single-blind, parallel-group trials, the RADMIS trials, investigating the effect of using the Monsenso system on a daily basis, this including an integrated feedback loop and context-aware CBT modules, compared with standard treatment in adult patients with unipolar disorder and bipolar disorder, respectively.

### Trial design and study organization

The RADMIS trials are randomized controlled, single-blind, parallel-group trials with a balanced allocation ratio (1:1) of adult patients with unipolar disorder or bipolar disorder stratified according to the psychiatric center from where the patients are discharged and the number of former hospitalizations (three or less or more than three). The included patients are randomized separately according to psychiatric diagnosis (unipolar disorder or bipolar disorder) to either active use of the Monsenso system (intervention group) or to standard treatment (control group). Thus, the RADMIS trials consists of two separate RCTs with two patient groups investigating the effect of the same intervention (the Monsenso system). The flow diagram of the RADMIS trials is presented in Fig. 2. The trails are conducted at the Psychiatric Center Copenhagen, Rigshospitalet, Copenhagen, Denmark. No changes in study design or methods have been made after trial commencement.

**Fig. 2 Fig2:**
[figure not shown]
Flow diagram of the RADMIS trials

### Participants and settings

Inclusion criteria: all patients over the age of 18 years with a unipolar disorder or bipolar disorder diagnosis, according to the *International Classification of Diseases, version 10* (ICD-10) using Schedules for Clinical Assessments in Neuropsychiatry (SCAN) [38], who are discharged from a psychiatric hospital in The Capital Region of Denmark during the period March 2017 to October 2018 following an affective episode (depression or mania) are invited to participate in the RADMIS trials. This corresponds to approximately 1200 patients with unipolar disorder and 600 patients with bipolar disorder per year. The mental health services in The Capital Region of Denmark covers a recruitment area of the Capital Region, Denmark, corresponding to 1.4 million people.

Exclusion criteria: patients who are pregnant and those who lack Danish language skills are excluded, since these factors may influence the possible effect of the RADMIS intervention.

### Study procedure

Potential participants are invited to participate in the RADMIS trials by contact with the staff during hospitalization. All potential participants who accept to meet with the RADMIS staff for further trial information are screened by trained researcher to make sure that they fulfil the criteria for participation, and are then included in the RADMIS trials. Following inclusion, baseline assessments are performed on all patients, and after these assessments the numbered opaque allocation envelopes are distributed by a research secretary ([name]) to the RADMIS study nurses. The included patients are randomized separately according to psychiatric diagnosis (unipolar disorder or bipolar disorder) to either the intervention group or the control group for a 6-month trial period.

An overview of the outcome assessments conducted by researchers blinded to intervention group is presented in Table 1. Information regarding the primary outcome, re-admissions and duration of re-admissions, will be obtained after completion of the two RCTs by linkage of the unique personal identification number (CPR) which is assigned to all 5.4 million persons living in Denmark [39] with the Danish Psychiatric Central Register [40].

**Table 1 Tab1:** Outcome assessments during the RADMIS trial

	SCAN and background information	Rating scales	Questionnaires	Clinical information
Baseline	x	x	x	x
Randomization to (1) smartphone-based monitoring and treatment (the intervention group) or (2) treatment-as-usual (the control group)				
3-month follow-up		x	x	x
6-month follow-up		x	x	x

*SCAN* Schedules for Clinical Assessment in Neuropsychiatry interview

Rating scales: Hamilton Depression Rating Scale 17-item (HDRS-17); Young Mania Rating Scale (only for patients with a bipolar disorder diagnosis); Psychosocial functioning test (Functional Assessment Short Test (FAST))

Questionnaires: perceived stress according to Cohen’s Perceived Stress Scale; quality of life according to the WHO Quality of Life-BREF (WHOQOL-BREF); self-rated depressive symptoms according to Beck’s Depressive Inventory (BDI); self-rated depressive symptoms according to the Hamilton Depression Self-rating Scale 6-item (HDRS-6); self-rated manic symptoms according to the Altman Self-rating Scale for Mania (ASRM) (only for patients with a bipolar disorder diagnosis); recovery according to the Recovery Assessment Scale; empowerment according to Rogers’ Empowerment Scale; adherence to medication according to the Medicine Adherence Rating Scale; wellbeing according to the WHO (five) Wellbeing Index; rumination according to the Rumination Response Scale (RRS); worrying according to the Penn State Worry Questionnaire (PSWQ); satisfaction according to the Verona Satisfaction Scale-Affective Disorder (VSS-A). The HDRS-6, the ASRM and the WHO (five) are filled out every month during the study 6-month period

Clinical information: re-admissions and duration of re-admissions (register data); number of affective episodes; number of contacts with clinicians and psychiatric emergency rooms; hospitalizations; medication, etc

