##### The integrated feedback loop between patients and clinicians

Study nurses with experience with unipolar disorder and bipolar disorder are assigned to the patients allocated to the intervention group of the RADMIS trials. The RADMIS study nurses are responsible for the integrated feedback loop. Patients allocated to the intervention group of the RADMIS trials will have the Monsenso application installed on a smartphone. The smartphone automatically transfers the self-monitored subjective measures and, for some smartphones, also the automatically generated behavioral data on measures of illness activity to servers at the hospital through secure connections (I-suite number RHP-2011-03). By giving informed consent to participate in the RADMIS, the patients allow for the RADMIS study nurses and their health care provider to access the monitored data through a secure web interface. The RADMIS study nurses go through the collected data approximately two to three times a week, or more often on patients where it is deemed necessary. A personal homepage is set up on a server allowing the patients to access all their own data through a similar secure web interface.The feedback loop on subjective measures: regardless the type of smartphone a feedback loop on the subjective measures is established. A standard of scoring thresholds for when the RADMIS study nurses initially should react was made. For example, the RADMIS study nurses react if the patients register ≥ −2 on the mood item for 2 days or more, or if the patients register changes in their sleep patterns of 1 h or more for more than 3 days. Following a run-in phase of approximately 2 to 4 weeks of self-monitoring, the patients and the RADMIS study nurses individualize the thresholds for when reaction should be made. Also the RADMIS study nurses and the patients agree on a concordance status in (a) the patients’ most important items for identifying prodromal symptoms of depression as well as (hypo)mania (only for patients with a bipolar disorder diagnosis), (b) the threshold for future early warning signs, and (c) actions to be taken in case of depression or (hypo)mania (only for patients with a bipolar disorder diagnosis)The integrated feedback loop on subjective and automatically generated behavioral data on measures of illness activity: a feedback loop integrating subjective and automatically generated behavioral data on measures of illness activity is established. The feedback loop integrates both subjective and automatically generated behavioral data on measures of illness activity in a flexible and adjustable model (a learning system) resulting in prediction analyses of the collected data providing messages for both the patients and the RADMIS study nurses such as: “You are invited to contact your RADMIS study nurse.”

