### Assessments

Researchers blinded to the patients’ allocation of intervention group ([name] and one other physician) who are not involved in the treatment of the patients carry out all outcome assessments. The unipolar disorder or bipolar disorder diagnoses according to ICD-10 are confirmed by a SCAN interview before inclusion of the patients. The patients are, regardless of randomization group, enrolled for a 6-month trial period and invited for outcome assessments by researchers blinded to intervention at baseline, after 3 months and after 6 months (Table 1).

At each visit with the researchers, the assessments include the following:

1. Clinician-administrated rating scales: the severity of depressive and manic symptoms (manic symptoms only assessed for patients with a bipolar disorder diagnosis) is measured using the Hamilton Depression Rating Scale 17-item (HDRS-17) [52] and the Young Mania Rating Scale (YMRS) [34], respectively, and psychosocial functioning is measured using the Functioning Assessment Short Test (FAST) [53]

2. Questionnaires: perceived stress according to Cohen’s Perceived Stress Scale [54], quality of life according to the WHO Quality of Life-BREF (WHOQOL-BREF) [55], self-rated depressive symptoms according to Beck’s Depressive Inventory (BDI) [56–58], self-rated depressive symptoms according to the Hamilton Depression Self-rating Scale 6-item (HDRS-6) [59], self-rated manic symptoms according to Altman Self-rating Scale for Mania (ASRM) (only for patients with a bipolar disorder diagnosis) [34], recovery according to the Recovery Assessment Scale [60], empowerment according to Rogers’ Empowerment Scale [61], adherence to medication according to the Medicine Adherence Rating Scale [62], wellbeing according to the WHO (five) Wellbeing Index [63], rumination according to the Ruminative Response Scale (RRS), worrying according to the Penn State Worry Questionnaire (PSWQ) [64], and satisfaction according to the Verona Satisfaction Scale-Affective Disorder (VSS-A) [65]. The patients are asked to fill out HDRS-6, ASRM (only for patients with a bipolar diagnosis) and WHO (five) every month during the 6-month trial period in both groups and in both trials.

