### Blinding

Owing to the type of intervention in the RADMIS trials, the patient, the patients’ health care provider and the RADMIS study nurses are aware of the allocated randomization group. The researchers responsible for outcome assessments, data entry, data analyses, interpretation of analyses and writing of papers are kept blinded to allocation at all times during the trial period, data analyses and interpretation of analyses. The trials are, therefore, single-blinded. The RADMIS study nurses do not collect any outcome measures. At each visit with the researchers, all patients are thoroughly instructed not to mention anything about randomization allocation. In case of unblinding of the included patients’ allocation status, one of the other researchers blinded to intervention in the RADMIS trials will conduct the outcome assessments.

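### As Table 1 reads, the blinded raters also gather counts of clinician contacts at 3 and 6 months, a question that only intervention patients could answer in a way that reveals their arm

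*Protocol article*

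**What the plan says.** **Who assesses.** Under Study procedure: "An overview of the outcome assessments conducted by researchers blinded to intervention group is presented in Table 1". Under Assessments, the blinded researchers are described as people "who are not involved in the treatment of the patients carry out all outcome assessments". The Blinding section adds that the study nurses collect no outcome measures.

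**What is assessed, and when.** Table 1 marks rating scales, questionnaires and clinical information at baseline, 3 months and 6 months. Its footnote defines clinical information as "re-admissions and duration of re-admissions (register data"), the number of affective episodes, and "number of contacts with clinicians and psychiatric emergency rooms; hospitalizations; medication, etc". The numbered list under Assessments, introduced by "At each visit with the researchers, the assessments include the following", names only the rating scales and the questionnaires.

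**What differs between arms.** Study nurses "are assigned to the patients allocated to the intervention group of the RADMIS trials". The section on the feedback loop says: "The RADMIS study nurses go through the collected data approximately two to three times a week". On signs of deterioration they contact the patient, and may direct the patient to the usual physician or another clinician.

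**Safeguards.** Under Blinding, at each visit "all patients are thoroughly instructed not to mention anything about randomization allocation". If a rater is unblinded, another blinded researcher takes over the assessments.

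**The concern.** HDRS-17, FAST and, in the bipolar trial, YMRS depend on the rater's judgement, and so do the episode counts built on the HDRS-17 and YMRS cut-offs. The Advantages section presents blinded rating of these secondary outcomes as a strength and contrasts it with the unblinded questionnaires.

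A question about contacts with clinicians, put by the rater, works against that strength. An intervention patient who answers fully may mention the study nurse; a control patient has no study nurse to mention. Any leak therefore runs in one direction. It also sets two requests against each other: keep silent about allocation, and report all clinician contacts.

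**Working it through.** No figure in the article is in dispute, so the check is mainly a comparison of sections, followed by an illustration of scale.

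**Step 1: do the raters gather the contact count?**
- For: the sentence introducing Table 1 assigns its content to blinded researchers; clinical information is marked at the same follow-up times as the scales; the register label is attached only to re-admissions and their duration; and no other collector is named, while the study nurses are ruled out.
- Against: the visit list under Assessments omits clinical information. Part of that column comes from a register after the trials end, so a mark at 3 or 6 months does not by itself show that a rater asked the patient.
- Result: collection by the raters is the natural reading, but it is not stated for this item.

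**Step 2: could the answer reveal the arm?**
- The Background, describing the group's pilot study, gives a nurse as an example of a clinician. The heading of the nurse-run feedback loop describes it as running between patients and clinicians.
- The contact count carries no definition that excludes study nurses, and none that includes them.
- Result: disclosure is plausible, and only from the intervention arm. The baseline visit carries no such risk because it precedes randomisation.

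**Step 3: how far do the safeguards reach?**
- The instruction covers allocation, but a patient may not see a contact count as a statement about allocation.
- Replacing the rater helps only when the disclosure is recognised, and it does not undo scores already given. Assessments identifies two assessors.
- Result: the risk is reduced, not removed.

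**Step 4: scale.** The inputs from the sample size section are SD 7 and 100 patients per arm. Assumed, not from the article: a share *u* of intervention patients is scored *s* points lower, controls are unaffected, and there is no true effect. The comparison is a simple two-sample one.

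- SE = 7 × √(2/100) = 0.99
- Shift in the arm mean: *b* = *u* × *s*
- Type I error = P(Z > 1.96 − *b*/SE) + P(Z < −1.96 − *b*/SE)

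| Share affected | *s* = 1 | *s* = 2 | *s* = 3 |
|---|---|---|---|
| 10% | 0.051 | 0.055 | 0.061 |
| 25% | 0.057 | 0.080 | 0.118 |
| 50% | 0.080 | 0.173 | 0.329 |

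Example: 50% and 2 points give *b* = 1.0 and *b*/SE = 1.01, hence 0.173. That shift is one third of the 3-point difference the article calls clinically relevant.

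As a side check on these inputs, a true 3-point difference has power of 85.8%, against the 80% stated. The stated figure is conservative on its own inputs, and this has no bearing on the present point.

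**The case against.** The strongest reply is that the article never says the raters ask this question. The visit list omits it, and another item in the same column comes from a register. Nor does the article say that study-nurse contacts are counted. In several places it lists the study nurses separately from the patient's health care provider. If the count means usual-care contacts, which exist in both arms, a truthful answer need not reveal anything. Two explicit safeguards are in place, the primary outcome does not pass through the raters, and a condensed article may leave the order of assessments to the full protocol.

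Much of this stands. It rules out several stronger readings that a reader might infer:
- that the raters are known to ask about contacts in the same interview: this is the natural reading of Table 1, not a statement;
- that the secondary outcomes are biased: only a risk is shown;
- that replacing an unblinded rater creates a rater difference between arms: the article gives no disclosure rate and no between-rater difference from which to judge this;
- that entering the satisfaction scale would unblind the raters: its items are not given, and the text does not show that the same person rates and enters data.

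The silence on order is not held against the article; ordering matters here only as part of the remedy. What the reply does not remove is the assignment itself. Table 1 as introduced gives blinded raters an item whose truthful answer may disclose allocation, and nothing in the text excludes study-nurse contacts from it.

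**Conclusion.** The point holds as a risk to the blinding of the rater-scored secondary outcomes in both trials. It rests on two readings: that the untagged clinical information in Table 1 is gathered by the blinded raters, and that patients may count the study nurse as a clinician. Both are well supported, and neither is explicit.

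The size is unknown. With disclosure in 10% of intervention patients, type I error stays at about 5% to 6%, which is negligible. At 50% it is 8% to 33%, which would matter. A reader might take the upper figure as the expected inflation, but the article supports no particular rate, and the upper figure needs half of the intervention arm to be scored 3 points lower. Results on re-admission are untouched, because they come from the register. This is a low-cost improvement that protects a strength the article claims, not a flaw that invalidates the design.

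**What to change.** 1. State that at each follow-up visit HDRS-17, FAST and, in the bipolar trial, YMRS are completed and locked before any service-use question.
2. Take the counts of clinician and emergency-room contacts away from the raters. Use a patient-completed form, collected and entered by non-rater staff already in the trial (the research secretary, for example), or use register data.
3. State that any contact count a rater sees excludes study-nurse contacts.
4. Bring Table 1 and the visit list under Assessments into line, naming the source and collector of the clinical information.

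The cost is a fixed order within the visit, one short form and a small shift of data entry to existing staff. Endpoints and sample size do not change. The downside is that self-reported counts may be slightly less complete than counts taken at interview.
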